#### Secondary Outcomes – Clinical

The secondary clinical outcomes include the Box and Blocks test, Upper Extremity Fugl-Meyer Assessment, the Patients' Structured Subjective Assessment, the EuroQol Five Dimensions Test and the National Institutes of Health Stroke Scale (NIHSS).

*Blocks and Box Test (BBT)* (41) is a unilateral assessment of gross manual dexterity. It can be used for a variety of neurological diagnoses including stroke. The subject is asked to move blocks (1" cube) from one compartment of the box to another compartment of equal size. The score is the maximum number of blocks that can be moved within 60 s.

*Upper Extremity Fugl-Meyer Assessment (FM)* (33) is an impairment based upper extremity measure consisting of 33 movements that test single and multi-joint movement in and out of synergy, digit individuation, speed, dysmetria, ataxia, and reflexes. Each item is rated on a three-point scale, 0 = cannot perform, 1 = performs partially, 2 = performs fully, for a total score of 66. Higher scores indicate less impairment and more isolated motions.

*Patient's Structured Subjective Assessment* (42) will be performed for the EVR and DVR groups. This is a 27-item questionnaire that addresses the subject's perception of the function of their hemiplegic arm and the effect this intervention had on their hand function. Subjects fill out the questionnaire prior to and directly after the intervention (ideally within 72 h). Some questions require a response such as disagree, neutral and agree, others require ordering their gaming activity preferences, or responding to a question with a short answer.

*EuroQo-EQ-5Dl* (43) is a self-rated health-related quality of life measure. Respondents rate themselves on five measures; (1). mobility (or ambulation), (2). self-care (bathing and dressing), (3). usual activities (their current function in “work, study, housework, family or leisure activities,” (4). pain/discomfort, and (5). anxiety/depression. The severity of each measure is rated as no problems, slight problems, moderate problems, severe problems, and extreme problems, with a 1-digit number describing the level selected for each measure. The five measurements are combined into a 5-digit number to describe the health state of the patient.

*National Institutes of Health Stroke Scale (NIHSS*). This 15-item scale evaluates the neurological status in stroke patients. Levels of consciousness, language, neglect, visual-field loss, extraocular movement, motor strength, ataxia, dysarthria, and sensory loss are each scored. The scores for each section range from 0 (normal) to 4.

#### Secondary Outcomes-Kinematic/Kinetic

*Secondary Outcomes-Kinematic/Kinetic* include maximum finger opening, active range of motion of the upper extremity, accuracy and coordination of active movement, measurements of force and force regulation, and a measure of coordination between hand transport and grasp during a reaching movement.

*Maximum pinch, lateral pinch, and whole hand grasping forces* will be measured using an ATI Nano17 force sensor. Further, to measure the ability to regulate pinch force, square, and sine waves will be presented on a computer screen. During square wave tracking, subjects will be asked to hold force for 12 s for a single repetition, at 10, 30, 40, 20, 30% of their maximum pinch force, continuously with 4 s rest between repetitions. During sine wave tracking, subjects will be asked to constantly adjust pinch force to follow a sine wave with frequency at 0.5 Hz and amplitude at 50% of maximum pinch force. Vertical position of the cursor on the screen will be defined by isometric force between the thumb and index fingertips measured by the force sensor. Root mean square error will be calculated to assess the accuracy of pinch force control.

*Active Range of Motion for fingers, wrist, elbow, and shoulder* will be measured using the CyberGlove and an array of motion sensors (TrackStar). *Maximum Finger Opening* will be estimated as the mean of the maximum active extension of the metacarpophalangeal (MCP) and proximal interphalangeal (PIP) joints for all five fingers. *Ability to Regulate Hand Opening/Closing* will be evaluated by measuring the accuracy of tracking a sine wave on the computer screen while the vertical position of the cursor is defined by the average of four MCP joints. The ability to regulate wrist flexion/extension, elbow flexion/extension, and shoulder abduction/adduction will also be evaluated separately using similar sine wave tracking. The wrist, elbow or shoulder angle will be used to define the vertical position of the cursor on the screen.

*Real-world Reach-Grasp Test* (44) will be used to measure the kinematics of everyday movements involving grasping and manipulating household objects. The goal of this outcome measure is to analyze whether the intervention training transfers to real-world reaching and grasping patterns of inter-finger coordination during pre-shaping of the hand, coordination between hand pre-shaping and transport of the hand to the target, and coordination of upper limb segments. Kinematics of reaching for an object, lifting it from the support, transporting it to a predefined location, and releasing the object will be evaluated.

The Reach-Grasp Test will be administered to the hemiparetic arm at each test point and the non-hemiparetic upper extremity once using an optical motion capture system (Optitrack Prime 13 cameras, Optitrack, USA). *Fifteen* active makers will be placed on each fingertip, metacarpophalangeal, and proximal interphalangeal joints. Additionally, 4 passive markers will be placed on the back of the hand, elbow, shoulder, and sternum. Subjects will be seated at a table with their hips and knees in a 90 degrees position. Their semi-pronated forearm and palm will rest on the table, with the hand positioned midline between the shoulders and 10 cm away from the chest. Test objects will be positioned at subjects' midline 20 cm from the subjects' hand. Subjects will be instructed to reach for an object, lift it from the support, transport it to a predefined location and release the object. Each reach will be repeated up to 10 times based on subject tolerance. OptiTrack motion capture software (Motive) will be used to record the marker coordinates. Hand peak velocity, time to peak velocity and movement smoothness of hand spatial trajectory will be calculated separately for all three sub movements: reaching to object, transporting object, and returning arm back to the starting position. Hand preshaping during reach will be analyzed as a measure of coordination between hand transport and grasp and will be used as a secondary kinematic outcome (44). Five objects include small (1 inch) and large (3 inch) cubes, small (2.5 inch diameter), and large (4.5 inch diameter) circular objects, and a small spray bottle (4 inch height).

*Robotic kinetic measures* will be collected to compare the immediate effects of training in the EVR and DVR groups. Subjects will perform a robot-based Arm Reaching test every other day immediately prior to VR/robotic training during the 10 days of training. Subjects will hold a robotic arm to reach 5 haptically rendered spheres located in a 3D virtual environment at various heights and depths to measure changes in elbow/shoulder range, velocity, and coordination.

*Measurement of Daily Use of Upper Extremity*. Activity monitors (GT9X Link, Actigraph) will be worn by the subject on both wrists for 24 h to quantify the daily use of the affected arm.

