#### Secondary Outcomes - Kinematic/Kinetic

For Aim 2 our initial statistical analysis will be applied to the vector of z-normed kinematic measures [Pinch Force Tracking Error, Maximum Pinch Force, Finger Flexion/Extension Tracking Error, Maximum Finger Opening], with fixed effects of Test Time and Treatment Group (EVR, DVR, DMUC and UC). *Post-hoc* comparisons will be analyzed through pre-planned contrasts. Separate analyses will be conducted for each output variable if appropriate. As exploratory analyses, the relationship between multiple output variables will be investigated using multiple-output-stacked mixed effects models.

Grasping of objects of various sizes and shapes will be analyzed (44). The subjects' ability to preshape their hands as it approaches the object to be grasped will be evaluated using support vector machine (SVM)-based classification analyses of the finger joints. Flexion/extension in the metacarpophalangeal and peripheral interphalangeal joints of the fingers plus finger abduction angles will be used as input variables. At each moment during reaching, the classification algorithm will predict which of the objects the subject is grasping in this particular trial. Classification error will be calculated as percent of trials where the algorithm made an incorrect prediction and will serve as an outcome measure, with smaller error values indicating better hand function. In addition to SVM, other classification methods will be investigated (e.g., linear discriminant analysis). The time profiles of the classification errors for grasping with the affected arm will be analyzed longitudinally. The time profiles of the magnitude of this classification error will be analyzed with mixed model analysis with fixed effects of Treatment Group (EVR, DVR, DMUC, UC), Test Time, Condition (either Object Size: Small, Large; or Object Shape: Round, Rectangular, Irregular) and Movement Time (5–95% epochs). Finally, classification error profiles obtained during grasping with the affected arm will be compared with the profiles of the less affected arm.

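### The grasp classification-error outcome can move with the number of reaches a patient tolerates, because nothing equalises trial counts across visits and arms

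*Protocol article*

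**What the plan says.** The Real-world Reach-Grasp Test is described under Measures, Secondary Outcomes-Kinematic/Kinetic. It uses five objects ("Five objects include small (1 inch) and large (3 inch) cubes", two circular objects and a spray bottle). On repetition the article says "Each reach will be repeated up to 10 times based on subject tolerance". It gives no minimum and no common number. The hemiparetic arm is tested at each test point and the other arm once. Hand preshaping is named there as a secondary kinematic outcome.

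The section Secondary Outcomes - Kinematic/Kinetic under Statistical Analysis defines the measure. On inputs: "Flexion/extension in the metacarpophalangeal and peripheral interphalangeal joints of the fingers plus finger abduction angles will be used as input variables". On the task: "At each moment during reaching, the classification algorithm will predict which of the objects the subject is grasping in this particular trial". On the outcome: "Classification error will be calculated as percent of trials where the algorithm made an incorrect prediction and will serve as an outcome measure", with smaller values read as better hand function. SVM is named, and other methods such as LDA are also to be explored. The error is analysed longitudinally with fixed effects that include treatment group and test time. In addition, "classification error profiles obtained during grasping with the affected arm will be compared with the profiles of the less affected arm".

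Neither section equalises the number of trials or adjusts for it. Neither says whether the classifier is trained on each patient's own session or on pooled data.

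**The concern.** A classifier with many inputs and few training trials makes more errors than the same classifier with more trials, even when the movements are equally distinguishable. If patients manage few reaches soon after stroke and more later, the error rate will fall over time for that reason alone, and the analysis will read the fall as better preshaping. If the less affected arm completes more reaches than the affected arm, the gap between limbs is inflated in the same way.

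This matters because the measure is meant to help separate recovered movement patterns from compensation, one of the questions listed under Anticipated Results. An artefact of trial count would look like recovery.

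**Working it through.** The article gives no error rate or power figure for this outcome, so there is no stated figure to reproduce. The check is a simulation of the mechanism.

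**Inputs from the article.** Five objects, so chance error is 1 − 1/5 = 80%. At most 10 repetitions per reach; read per object, that is at most 5 × 10 = 50 reaches per session.

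**Assumptions.** 14 inputs (5 metacarpophalangeal + 5 proximal interphalangeal + 4 abduction angles; the article gives no count). Trial data are Gaussian: x = μ_k + e, with e of unit SD in each input and object means μ_k drawn with SD s (the separation). Here s is 0.3, 0.5 or 0.8 and does not change with n, the number of trials per object, so true preshaping is constant. The classifier is trained within the session and scored leave-one-out: error = misclassified trials / (5n). With n = 3 each prediction rests on 15 − 1 = 14 training trials for 14 inputs; with n = 10 it rests on 50 − 1 = 49.

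**Results: expected error at n = 3, 5 and 10**

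| s | Classifier | n = 3 | n = 5 | n = 10 | Fall 3→10 | Fall 5→10 |
|---|---|---|---|---|---|---|
| 0.3 | SVM | 0.811 | 0.715 | 0.675 | 13.6 points | 4.0 |
| 0.5 | SVM | 0.595 | 0.499 | 0.514 | 8.1 | −1.5 |
| 0.8 | SVM | 0.331 | 0.242 | 0.228 | 10.3 | 1.4 |
| 0.3 | LDA | 0.759 | 0.712 | 0.637 | 12.2 | 7.5 |
| 0.5 | LDA | 0.668 | 0.554 | 0.425 | 24.3 | 12.9 |
| 0.8 | LDA | 0.428 | 0.310 | 0.181 | 24.7 | 12.9 |

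LDA (with shrinkage) used 300 replicates per cell and SVM only 25, so the SVM figures are noisy. At s = 0.5, for example, the Monte Carlo standard error of the SVM fall from 3 to 10 is √(0.168²/25 + 0.070²/25) ≈ 0.036, or 3.6 points.

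**Sensitivity to settings.** A further held-out LDA run gave 71%, 68% and 62% at s = 0.3; 59%, 51% and 41% at s = 0.5; and 34%, 25% and 16% at s = 0.8. The falls from 3 to 10 are 9, 18 and 18 points, so the LDA range over all runs is about 9 to 25. Another SVM run at s = 0.5, with 250 replicates, gave 0.565, 0.500 and 0.460, a fall of 10.5 points from 3 to 10 and 4.0 from 5 to 10.

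**Scored on training trials instead.** At s = 0.5 LDA error was 0%, 3% and 12%, so the artefact reverses direction.

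**Classifier that does not depend on the session's own count.** Using the true object means, error was 0.276 at n = 3 and 0.273 at n = 10 (s = 0.5), and 0.086 and 0.083 (s = 0.8). The mean does not move; only precision does (SD 0.119 against 0.075 at s = 0.5).

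**Equalised trials.** At s = 0.5, 10-trial sessions subsampled to 5 per object gave 49.5% error, against 50.6% for true 5-trial sessions. Subsampling removes the shift.

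**The case against.** The strongest objection is that the article never says the classifier is trained on the patient's own session. Training and validation settings are details that a condensed article may leave to the full protocol, the analysis plan or the cited method, so their absence is no fault. This stands, and it makes the point conditional: with a classifier independent of the patient's count there is no shift in the mean. Within-session training remains the likelier reading, because the algorithm identifies the object a given subject is grasping and profiles are compared between a subject's two arms.

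Second, the article gives no data on tolerance. That counts start low and rise, or are higher in the less affected arm, is plausible but assumed. The 3-to-10 change is an extreme case, and for SVM, the classifier the article names, the 5-to-10 change is small. This also stands.

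Third, a reader might infer that the treatment comparison itself is biased. The documents do not support that in general. Groups are randomised within impairment and MEP strata, and the 4-month visit is at a common time after stroke, so tolerance that grows with recovery should affect all groups alike unless treatment changes the number of reaches managed. What remains is narrower. The a priori contrasts use Pre, and Table 2 notes that the delayed group has two Pre tests. If the one just before delayed training serves as Pre, the early group's Pre falls sooner after stroke than the delayed group's, and trial counts could differ.

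Finally, the measure is one secondary outcome among many and is not in the initial vector of kinematic measures for Aim 2. That limits its importance without removing the problem.

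**Conclusion.** The point holds in conditional form. The article lets trial count vary with tolerance for an outcome that, under the likely training scheme, depends on that count. With preshaping unchanged, going from 3 to 10 trials per object lowers expected held-out error by about 8 to 14 points (SVM) or 9 to 25 points (LDA); for SVM from 5 to 10 the change is about 4 points or less. These sizes rest on the assumed 14 inputs, Gaussian noise, three separations and within-session training. The realised bias is unknown because no trial counts are given.

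The exposure is mainly in the Test Time effect and the affected versus less affected arm comparison. Group contrasts are exposed only where counts differ between groups. It would be too strong to say that the outcome is certainly biased or that the randomised comparison at 4 months is invalid. ARAT and the sample size are untouched.

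**What to change.** In the Statistical Analysis section on kinematic/kinetic outcomes, take one of two routes.

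- **Equalise the trials.** Compute error on held-out trials only, using the same number of trials per object for every visit and both arms. Subsample each session repeatedly to that number and average. Name SVM as the single outcome classifier and keep other methods as sensitivity analyses.
- **Decouple the classifier.** Use one whose training does not depend on the patient's own session count, and say so.

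Under the first route, choose a low common number so that few sessions fall short of it. Do not simply exclude those that do. They probably come from the most impaired patients, and under the listwise exclusion in Management of Missing Data and Dropouts their loss would be informative. Report trial counts by group, visit and arm, and bring low-count sessions into a sensitivity analysis, for example one that adjusts for trial count.

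The cost is analysis code, with no new data. Some trials go unused in each subsample, so precision is slightly lower. Under the second route, precision still varies with trial count although the mean does not.

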### Randomization and Recruitment

An independent statistician will generate the randomization sequence prior to initiation of the study. Physicians and therapists will identify potential subjects. The study coordinator will contact the patients as soon as they are medically stable, inform them about the study, screen them for inclusion and exclusion criteria and enroll them. The subjects will be stratified on two dimensions, impairment level and presence or absence of Motor Evoked Potentials (MEPs). Prior to randomization, potential subjects will be assessed using the Upper Extremity Fugl-Meyer Assessment (FM) (33) to establish motor impairment level, and Transcranial Magnetic Stimulation (TMS) for the presence or absence of MEPs in the lesioned hemisphere. These scores will be used to stratify subjects into four subgroups; (1) Severe, FM score 10–19, MEP+, (2) Severe, FM score 10–19, MEP–, (3) Moderate, FM score 20–49, MEP+, (4) Moderate, FM score 20–49, MEP-. If a subject is not eligible for TMS, he/she will be assigned to either group 2 (if severe) or group 3 (if moderate). This is based on the Stinear et al. (34) study in which study subjects with moderate impairment all had MEPs (34). Stratified block randomization will then be used to achieve a balanced assignment (35). For each of the four subgroups, every 4 subjects are one block. In each block, there is one subject for each type of treatment. One hundred twenty subjects will be assigned sequentially to four types of treatment groups (30 per group): (a) state-of-art usual care only (UC), (b) usual care plus an additional 10 h of usual care (dose-matched usual care, DMUC; initiated 5–30 days post-stroke), (c) usual care plus an additional 10 h of intensive therapy focusing on the hand using robotically facilitated rehabilitation interventions presented in virtual environments initiated **early** (5–30 days post-stroke) (EVR), and (d) usual care plus an additional 10 h of intensive therapy focusing on the hand using robotically facilitated rehabilitation interventions presented in virtual environments initiated later (30–60 days post stroke) (DVR) (see Figure 1).

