### Eligibility

Studies in the chronic and early subacute phase post-stroke have consistently demonstrated the adaptability and flexibility of the *NJIT-RAVR* robotic/VR system, thus allowing for broad inclusion criteria (36, 37). We are including subjects 30–90 years old, able to follow instructions, with severe to moderate arm weakness (≥10/66 and ≤49/66 FM score), and intact cutaneous sensation. Individuals with UEFMA scores <10 will not be included as they will not have the motor ability to utilize the system effectively. Patients will be excluded from the study if they were not independent prior to the stroke, are too ill to tolerate training, have persistent motor impairment from prior stroke, have aphasia or spatial neglect precluding their performing the tasks or following task instructions, have ≥1 on the NIHSS limb ataxia item, severe proprioceptive loss, ≥3 on the Modified Ashworth Scale (of the elbow, wrist, or finger flexors), or a previous medical history of neurological deficits or orthopedic conditions that limit arm and hand movement.

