#### Management of Missing Data and Dropouts

Besides listwise exclusion, which assumes missing data completely at random, multiple imputation methods will be used as a sensitivity analysis to examine the effect of different assumptions about missing data.

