## Discussion

This study focuses on arm and hand rehabilitation that (1) can be delivered in an inpatient rehabilitation facility during the early period of heightened neuroplasticity using VR/robotic simulations to facilitate the delivery of increased intensity of an intervention, (2) can quantify intensity to distinguish between total therapy time and actual movement time, (3) can specifically target the particular movement deficits that need to be modified, and (4) can incorporate patients with minimal movement. Independent upper extremity function is critically important to restore full independence and reduce the need for costly supportive care. One of the issues that may contribute to less than satisfactory outcomes for the hand (as well as the arm) is the complexity of hand motor control that involves coordination of multiple degrees of freedom. Early hand therapy is often limited when patients have not recovered sufficient motor function to utilize the hemiparetic hand during functional activities. Frequently therapists train compensatory movements using the less affected upper extremity, in an effort to attain maximal independence prior to patient's discharge in the face of the ever-decreasing length of stay in inpatient rehabilitation as part of a stroke care plan. This VR/robotic system is well-suited for the delivery of hand and arm training for more affected patients. Sensory and perceptual affordances provided by the integration of VR and robotics can target the unique hand deficits that one cannot address in real-world therapy (37), and thus possibly allow for functional improvement to move beyond the spontaneous recovery predicted in the literature (62).

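### Transport and return kinematics of the Reach-Grasp Test do not exist for a patient who cannot grasp, and listwise exclusion then compares arms in a subset selected partly on treatment response

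*Protocol article*

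**What the plan says.** All references are to the protocol article.

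- **Who is enrolled.** Under Randomization and Recruitment, patients are classed by Fugl-Meyer score and motor evoked potentials: "These scores will be used to stratify subjects into four subgroups". Two of the four are severe, with scores of 10–19. The floor of 10 under Eligibility is justified by ability to use the robot, not by ability to grasp a real object: "Individuals with UEFMA scores <10 will not be included as they will not have the motor ability to utilize the system effectively".
- **What the test asks.** Under Secondary Outcomes-Kinematic/Kinetic: "Subjects will be instructed to reach for an object, lift it from the support, transport it to a predefined location and release the object". There are five objects, the largest a 3 inch cube and a 4.5 inch circular object. Each reach is repeated up to 10 times as tolerated, with no minimum. The affected arm is tested at every assessment, including the early pre-test.
- **What is scored.** "Hand peak velocity, time to peak velocity and movement smoothness of hand spatial trajectory will be calculated separately for all three sub movements". The three are reach, transport and return. Preshaping during reach is separately named as a secondary kinematic outcome.
- **How data are analysed.** Statistical Analysis gives a mixed model with treatment group, test time and their interaction, and the baseline value as covariate.
- **What happens to missing values.** Management of Missing Data and Dropouts begins: "Besides listwise exclusion, which assumes missing data completely at random". It adds multiple imputation as a sensitivity analysis.

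**The concern.** A missing transport measure can mean two different things. The patient may not have been assessed, in which case a value exists but was not seen. Or the patient was assessed and could not lift the object, in which case no value exists and the inability is itself the result. The stated rule treats both as missing completely at random.

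After randomisation, inability to grasp depends on recovery, which the treatment is meant to change. If one arm restores grasp in more patients, its extra completers tend to be the weaker performers, and they lower that arm's mean. The other arm loses the corresponding patients from its mean. The randomised comparison is no longer protected, and the distortion works against the more effective arm.

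The baseline covariate adds a second loss. A patient unable at Pre has no baseline value and drops out even if grasp is present at 4 months, which is among the clearest forms of recovery the trial could observe.

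**Working it through.** **1. The plan's own figure.** The article gives no sample size, effect size or rate of inability for the Reach-Grasp measures. Its contrast sample size for the ARAT (24 per group, Cohen's f = 0.42) reproduces: noncentrality 0.42² × 48 = 8.47 on 1 and 46 degrees of freedom gives 81.3% power at alpha 0.05. The article states no power; 80% is assumed as the target. The present point does not depend on that figure.

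**2. Which measures can be undefined.**

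| Measure | Needs grasp and lift? | Affected |
|---|---|---|
| Reach-phase velocity, timing, smoothness | No, only a reach towards an object 20 cm away | Not in this way |
| Preshaping during reach (classification error) | No, taken before the grasp | Not in this way |
| Transport-phase kinematics | Yes | Yes |
| Return-phase kinematics after release | Yes | Yes |
| z-normed Aim 2 vector (two pinch-force and two finger-movement measures) | Not from this test | Not in this way |
| ARAT | No movement scores 0 | No |

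A patient may bring the arm back after a failed reach, but that is a different movement from a return after release.

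**3. Who is dropped.** Unable at Pre and able at 4 months: dropped, because the covariate is absent. Able at Pre and unable at 4 months: dropped, because the outcome is absent. Unable at both: dropped. Only patients able at both are compared.

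**4. Size, on assumed inputs.** None of these inputs is in the article. Let ability be normal with SD 1, with mean 0 in control and 0.50 in the better arm. Let the kinematic score have SD 1, a true arm difference of 0.50 and correlation r with ability within arm. A value exists only above a cut c.

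With 30% of controls unable, c = Φ⁻¹(0.30) = −0.524.

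- Control: share able 0.700; λ₀ = φ(−0.524)/0.700 = 0.497.
- Better arm: cut relative to its mean −1.024; share able 0.847; λ₁ = φ(−1.024)/0.847 = 0.279.
- Difference among completers = 0.50 + r(λ₁ − λ₀) = 0.50 − 0.218r.
- Variance of ability among completers, 1 + aλ − λ² (a = cut relative to the arm mean): 0.493 and 0.637. The score variance is r² times this plus 1 − r², pooled by the shares able.

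| r | Difference, full-population SD | Completers' pooled SD | Difference in completers' own SD | Lost from 0.50 |
|---|---|---|---|---|
| 1.0 | 0.282 | 0.756 | 0.37 | 25% |
| 0.7 | 0.347 | 0.889 | 0.39 | 22% |
| 0.5 | 0.391 | 0.945 | 0.41 | 17% |

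For r from 1.0 down to 0.5, the same formulas give 0.40 to 0.43 with 20% of controls unable and 0.35 to 0.40 with 40% unable, again in the completers' own SD.

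**5. A second assumed model.** A simulation took a severe share of 20–60%, half of severe controls able, an ability shift of 0.3–0.6 SD and a correlation of 0.5–0.7. Values existed for 67–85% of controls and 76–93% of treated patients. With no true kinematic effect, the completers-only comparison was biased by −0.04 to −0.18 SD against the better arm. True effects of 0.14–0.39 SD appeared as 0.07–0.28 SD. These are full-population SD units.

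**The case against.** Several objections limit the point.

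- **Scope.** A reader might infer that all Reach-Grasp outcomes exist only in patients who recover grasp. The article does not support that: reach-phase kinematics and preshaping need only a reach. A patient who reaches without shaping the hand still yields joint angles, so poor function can be scored. A reader might also infer that Aim 2 rests on these measures. The initial Aim 2 analysis is a vector that contains no Reach-Grasp measure, and the only Reach-Grasp arm comparison spelled out is preshaping classification error. For velocity, timing and smoothness, an arm comparison follows only from the general mixed-model text.
- **Evidence of inability.** The Discussion says "Early hand therapy is often limited when patients have not recovered sufficient motor function to utilize the hemiparetic hand during functional activities", but this concerns early therapy in general, not the 10–19 strata or this test. The statement that the approach "can incorporate patients with minimal movement" describes the assisted robotic training. The objects also include a 1 inch cube. Inability in the severe strata is a plausible inference and is not quantified.
- **Imputation.** The article does offer multiple imputation to vary the missing-data assumption, and non-parametric mixed models if normality fails. Neither defines a result for a movement that did not occur.
- **Deferred detail.** Scoring of failed trials on one secondary test is commonly left to the full protocol or analysis plan. That would settle the matter if the article were silent. It is not: it states listwise exclusion under MCAR and a baseline covariate, and those stated rules produce the selection.

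The objections on scope and evidence stand and are reflected here. Those on imputation and deferred detail do not remove the problem.

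**Conclusion.** The point holds for the transport and return kinematics and for the listwise rule applied to them. Any arm comparison of these secondary measures would be made among patients selected partly on treatment response, and patients unable at Pre who later recover would be lost. Inability at the first pre-test is not itself a treatment response; the harm there is exclusion.

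The size cannot be known from the article. With 30% of controls assumed unable, a true 0.50 SD shows as about 0.37 to 0.41 in the completers' own SD, a loss of roughly 17–25% for correlations from 0.5 to 1. A reader who took the 0.28 SD from the perfect-correlation case could infer a loss of about 43%. That figure is in full-population units; completers vary less, so the standardised loss is nearer 25% even in that extreme case. Under the assumed models the bias runs towards zero when there is a true effect and against the better arm when there is none. The primary ARAT conclusion is unaffected.

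**What to change.** Under the Reach-Grasp Test, the kinematic analysis section and the missing-data section:

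1. Record, per object and visit, whether the task was completed or attempted but unable, separately from a visit not attended.
2. Report completion by arm and visit.
3. For transport and return measures, replace listwise exclusion with an analysis of all assessed patients: ranks with unable as the worst rank, at baseline as well as follow-up, or a two-part analysis of completion and of quality given completion. State in advance which end of each measure is worse. Visits not attended remain missing.
4. Show the completers-only result beside it, labelled supportive.

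The cost is one recorded field and some analysis wording. The field is best captured prospectively; Current Results reports seven subjects already through the 6-month test, for whom it would have to come from the test records if these allow. The drawback is that a worst-rank composite mixes ability to do the task with quality of movement, which is why both results should be shown.
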